## Abstract

**Introduction:**

Small renal masses (SRMs; ≤4 cm) account for two-thirds of new diagnoses of kidney cancer, the majority of which are incidental findings. The natural history of the SRM seems largely indolent. There is an increasing concern regarding surgical overtreatment and the associated health burden in terms of morbidity and economy. Observational data support the safety and efficacy of percutaneous cryoablation but there is an unmet need for high-quality evidence on non-surgical management options and a head-to-head comparison with standard of care is lacking. Historical interventional trial recruitment difficulties demand novel study conduct approaches. We aim to assess if a novel trial design, the cohort embedded randomised controlled trial (RCT), will enable carrying out such a comparison.

**Methods and analysis:**

Single-centre prospective cohort study of adults diagnosed with SRM (n=200) with an open label embedded interventional RCT comparing nephron sparing interventions. Cohort participants will be managed at patient and clinicians’ discretion and agree with longitudinal clinical data and biological sample collection, with invitation for trial interventions and participation in comparator control groups. Cohort participants with biopsy-proven renal cell carcinoma eligible for both percutaneous cryoablation and partial nephrectomy will be randomly selected (1:1) and invited to consider percutaneous cryoablation (n=25). The comparator group will be robotic partial nephrectomy (n=25). The primary outcome of this feasibility study is participant recruitment. Qualitative research techniques will assess barriers and recruitment improvement opportunities. Secondary outcomes are participant trial retention, health-related quality of life, treatment complications, blood transfusion rate, intensive care unit admission and renal replacement requirement rates, length of hospital stay, time to return to pre-treatment activities, number of work days lost, and health technologies costs.

**Ethics and dissemination:**

Ethical approval has been granted (UK HRA REC 19/EM/0004). Study outputs will be presented and published.

**Trial registration:**

ISRCTN18156881; Pre-results.

Strengths and limitations of this studyThe main strength of this study is the use of a novel and pragmatic trial design, the cohort embedded randomised controlled trial, to improve participant recruitment.Trial recruitment difficulties have hindered the acquisition of level one evidence on interventional management of small renal masses (SRMs), so the study will also incorporate qualitative research techniques to assess barriers and recruitment improvement opportunities.Possible study limitations include the lack of generalisation of results to individuals with large renal masses or advanced disease; the open label nature of the trial’s interventional comparison and the feasibility study being single site.If the primary outcome (successful recruitment) is met, this will enable the implementation of a larger-scale multicentric cohort embedded randomised trial to compare percutaneous cryoablation to robotic partial nephrectomy as a management strategy for SRMs.

## Introduction

Over 12 000 patients are diagnosed with renal cancer in the UK every year,^1^ and the incidence is increasing by 2% annually.^2^ The number of kidney cancer cases has more than doubled since the 1970 s^1^. Small renal masses (SRMs; T1a lesions on Tumour Node Metastases (TNM)staging; ≤4 cm of largest axis) account for two-thirds of new diagnoses of kidney cancers,^3^ the majority of which are incidental findings on investigations for other ailments or non-specific symptoms.^4^

The natural history of the SRM seems largely indolent. It is known that some (up to 40%) do not grow, and the majority that do increase in size, tend to enlarge slowly, between 1 and 15 mm per year, and providing that they do not breach the 4 cm size threshold, pose a very low risk of metastasis (1%).^5 6^ Treatment options for SRMs include active surveillance, ablation (either cryoablation or radiofrequency ablation) or surgical excision (partial nephrectomy or radical nephrectomy).^7^

The mainstay in treatment of a SRM is partial nephrectomy.^7^ Partial nephrectomy is recommended whenever technically possible as it preserves kidney function while providing good long-term oncological control. However, it is complex surgery and is associated with a higher major complication rate (4.9%), compared with radical nephrectomy (1.3%).^8^ In most cases, partial nephrectomy is performed using the da Vinci surgical robot system which costs around £1.5–2 million to purchase. Robot-assisted partial nephrectomy is estimated to cost between £7000 and 11 900 per case once the purchase and maintenance of the robot are taken into account.^9^

Considering the slow growth and indolent nature of the majority of SRMs, there is an increasing concern regarding overtreatment with surgery and the associated health burden both in terms of morbidity and economy. An alternative treatment option that also preserves renal function for SRMs is cryoablation which is now almost exclusively performed percutaneously under CT guidance. Cryoablation uses argon probes to freeze and kill the tumour, and is performed under a short general anaesthetic, usually with a single night admission. Present guideline recommendations for clinical practice are based on low-level evidence (level of evidence is 3 based on the Oxford Centre for evidence-based medicine system) and advocate cryoablation for elderly patients, or those with significant comorbidities due to the increased morbidity associated with surgical excision.^7^ Cryoablation is also an attractive option for patients with familial or sporadic multifocal bilateral tumours, as an alternative to multiple repeated surgical procedures and to increased renal function preservation compared with partial nephrectomy. Longer-term oncological outcomes from cryoablation are emerging and indicate equivalent oncological control at 9 years when compared with partial nephrectomy—this means that the distinction in patient selection criteria for cryoablation or for partial nephrectomy is becoming less clear.^10^ A recent large retrospective study at the Mayo Clinic (USA) reported that recurrence-free survival was similar for both partial nephrectomy and cryoablation.^11^ Overall survival was superior after partial nephrectomy, but this is likely due to selection bias as patients who underwent partial nephrectomy were significantly younger and had lower Charlson comorbidity scores.^11^

A recent systematic review of cryoablation for SRM reports on the excellent functional outcomes, rapid recovery and low rates of complications, supporting its use as an alternative minimally invasive treatment modality.^12^ Cryoablation can also be performed at a significantly lower cost than partial nephrectomy. Direct comparison studies in the UK are not yet available, but a study in Michigan, USA, reported the mean total cost for percutaneous cryotherapy to be almost half the cost of open or robot-assisted partial nephrectomy: $6067 versus $11 392 or $11 830 (p<0.0001).^13^

Previous attempts of randomised controlled trials (RCTs) in the context of SRM, for example CONSERVE (A feasibility study for a multicentre randomised controlled trial to compare surgery (partial nephrectomy) with needle ablation techniques (radiofrequency ablation/cryotherapy) for the treatment of people with small renal masses (4cm)) (comparing partial nephrectomy with radiofrequency or cryoablation; ISRCTN23852951) and SURAB (Study comparing ABlation with active SURveillance, in the management of incidentally diagnosed small renal tumours: a feasibility study) (comparing active surveillance and cryoablation; ISRCTN31161700) were not completed. This has been due to a number of factors, most notably; delays in obtaining National Health Service (NHS) permissions for multicentre sites, delays in treatment in the ablative arms due to lack of radiological capacity and insufficient trial duration (24 months for CONSERVE). Overall, CONSERVE involved four sites with a target of 60 participants and recruited 17. SURAB was stopped early due to the recruitment of only five patients when they had predicted 32 by a pre-defined milestone time point.

This means that we currently do not know how best to advise our patients other than by presenting clinical outcome variables of hospital stay and recovery. Current evidence available on the treatment outcomes of SRMs now point to a situation of clinical equipoise between partial nephrectomy and cryoablation, and well-designed clinical trials are crucial to clarify the treatment strategy, minimise overtreatment and improve overall patient outcome. This has been identified as a priority area by the renal cancer subgroup of the National Cancer Research Institute.^14^

Surgical RCTs are notoriously challenging to design and deliver. The main obstacles include professional resistance due to a perceived lack of clinical equipoise, lack of ability to ‘blind’ treatment allocation and an inherent and understandable reluctance for patients to accept treatment allocation based on chance alone. An alternative trial design for effective comparison of treatments has been reported, the ‘cohort embedded RCT’ and has been used successfully in chronic obstructive pulmonary disease and colorectal cancer trials.^15 16^ While informed consent is regathered for the intervention trial, the data from the cohort are based on prior broad consent. Unlike the traditional RCT design, the control participants are informed about prospective relevant trials within the cohort.^17^

The proposed cohort embedded RCT study design fully incorporates recruitment intervention techniques to pre-empt and identify recruitment issues early, ensuring successful delivery of both the initial feasibility trial and full trial. Qualitative research has been shown to improve recruitment in RCTs.^18^ The study design also allows the future addition of further intervention arms, that is, multiple RCTs can be embedded in the study cohort (subject to separate ethics approval). The advantages are that long- and short-term outcomes can be measured and compared, and natural history of the condition can also be studied. Important additional advantages include the fact that patients know which treatment they are agreeing to, the non-disruptive nature of the trial as patients receive care in routine healthcare settings and large numbers can be recruited. We conducted an online survey together with the charity Kidney Cancer UK to ascertain broad acceptability of the study’s design and willingness of patients to be recruited into nephron sparing treatment (NEST; unpublished data). Over a 2-week period, there were 99 respondents. Ninety per cent of patients indicated willingness to be followed up for life and 99% indicated that they would consent to being approached in the future if there was a new treatment or test. Ninety-nine per cent would consent for patient report outcome measures (PROMs)/questionnaires to be sent (maximum two per year), 98% would consent for blood and urine to be used for research and 99% would consent for tissue to be used for research. This online survey suggests strong support and need from the kidney cancer patient community for the broad concepts of the study.

The overarching objective of this feasibility study is to ascertain if a novel cohort embedded RCT design with recruitment improvement strategies can deliver a full-scale interventional trial comparing nephron sparing interventions in kidney cancer.

## Methods and analysis

This report complied with Standard Protocol Items: Recommendations for Interventional Trials guidelines^19^ (online supplementary document 1).

10.1136/bmjopen-2019-030965.supp1Supplementary data

### Study design

Single-centre prospective feasibility cohort study of adults that have been diagnosed with a SRM (n=200) with an open label embedded interventional RCT comparing nephron sparing techniques (figure 1 – Trial flow chart).

**Figure 1 F1:**
[figure not shown]
Study flow chart.

This pragmatic study design incorporates a two-stage consent process:The first stage allows the creation of a prospective observational cohort of patients with SRMs. Cohort participants will be managed at patient and clinicians’ discretion and consent for: (a) long-term follow-up and data linkage to NHS digital and/or other central NHS registries; (b) future randomised invitation for new interventions, tests, or treatments; (c) participation in interventional trials as a control group without need of further consent; (d) PROMs/questionnaires completion; and (e) biobanking of blood/urine/tissue.In the second stage, cohort participants with biopsy-proven renal cell carcinoma (RCC) who are eligible for both percutaneous cryoablation and partial nephrectomy will be randomly selected (1:1) and invited to consider percutaneous cryoablation (n=25). Participants randomly selected to consider the trial intervention (percutaneous cryoablation) will be asked for informed consent (second consent process) and will form the interventional arm. Participants not randomly selected to consider the trial intervention will receive standard of care (partial nephrectomy) and will form the control arm. By virtue of having agreed to be part of control trial arms at the first stage consent process, these participants will not require a second consent process. They will, however, be subject to surgical consent for the procedure as part of standard practice.

Patient information sheets and consents forms are available in online supplementary document 2 to 5.

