### Interventions

Cohort participants eligible for the embedded RCT will be randomised 1:1 and invited to consider the trial intervention (percutaneous cryoablation). Randomisation will be performed in blocks of 10 participants through the online system ’Sealed Envelope' (www.sealedenvelope.com) to ensure allocation concealment. This will be an open label trial with unblinded outcome assessment.

The control group will be composed of participants treated with standard of care (partial nephrectomy). The trial intervention will be performed by interventional radiologists under CT guidance using argon probes to freeze and kill the tumour. The standard of care will be performed by urological surgeons with da Vinci robot assistance.

No restrictions will be placed on other clinically necessary concomitant care. Follow-up for the purposes of this feasibility trial will be 6 months, but standard clinical follow-up will be at least 5 years (table 1—visit schedule and assessments). On average, patients attend two clinic appointments prior to treatment. Post-treatment follow-up is based on histological findings at biopsy/surgery but usually involves 6 monthly clinic visits for a minimum of 5 years. Participants will not be required to have any additional visits, apart from volunteers for focus groups and structured interviews.

**Table 1 T1:** Visit schedule and assessments

Procedures	Visits								
	Screening	Baseline	Intervention	Week 4 post-intervention (only second stage of study)	Month 6 after baseline (first stage of study) or intervention (second stage of study)	Y1	Y2	Y3	Y5
Demographics		X							
Medical history		X							
Physical examination		X		X					
Consent		X	X						
Blood test		X		X	X	X	X	X	X
Imaging	X				X	X	X	X	X
Questionnaire		X		X	X	X	X	X	X
Cryoablation or partial nephrectomy			X						
Case report form		X	X	X	X	X	X	X	X
Adverse event reporting		X	X	X	X	X	X	X	X
Biobanking of blood/urine/tissue		X	X	X	X	X	X	X	X

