### Sample size and recruitment

The aim of this study is to assess the feasibility of a large definitive trial comparing partial nephrectomy and percutaneous cryoablation in the treatment of SRM and to inform the design, sample size and outcome measures for a subsequent large multicentre prospective trial, so formal sample size calculations are inappropriate. We will aim to recruit 50 patients into the embedded randomised study, randomised equally between the two groups. This sample size will allow the assessment of whether the consent rate of 30% has been achieved with a 95% CI of ±11%. Sample sizes between 24 and 50 have been recommended to estimate the SD required for sample size calculation to allow design of a full trial.^20 21^ We anticipate being able to recruit at least 30% of eligible patients which equates to 25 patients annually, and a total recruitment time of 24 months.

Recruitment issues will be pre-empted and identified early by the qualitative researcher and their team, ensuring successful delivery of both the initial feasibility trial and full trial. This will include participant involvement in semistructured interviews and focus groups to explore views on the presentation of the study information, understanding of the trial process and reasons underlying decisions to accept or decline the trial. As part of the qualitative research effort, participants who volunteer to take part in structured interviews and focus groups will be asked to participate in additional visits. Trial management group members and clinician involvement will also take part in semistructured interviews to explore their perspectives on the study design, and their experiences with recruitment.

If interim analysis after 12 months of initiation of recruitment shows evidence of any of the following:consent rate of <30%,cryoablation results in more than a 50% increase in complications compared with partial nephrectomy at 90 days,the intervention results in more than a 50% increase in waiting time for treatment compared with the standard treatment group, then a detailed ‘plan of action’ will be formulated together with the qualitative research team to identify any areas in the recruitment/study pathway that can be improved. A detailed report will be presented to the Sponsor, Trial Steering Committee and the Data Monitoring Committee. If no remedial actions are deemed suitable, then the trial will be stopped.

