### Statistical methods

This is a feasibility study; therefore, all analyses should be considered exploratory. Data will be analysed on an intention-to-treat basis.

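### Arm membership is stated inconsistently: by random selection, by treatment received and possibly by second consent, and patients who decline cryoablation are placed in no arm

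*Protocol article*

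**What the plan says.** All places are in the protocol article.

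- **Order of events.** Interventions: "Cohort participants eligible for the embedded RCT will be randomised 1:1 and invited to consider the trial intervention (percutaneous cryoablation". Random selection therefore precedes the second consent.
- **Interventional arm.** Study design (two-stage consent text): cohort patients eligible for both treatments "will be randomly selected (1:1) and invited to consider percutaneous cryoablation (n=25"). Those selected "will be asked for informed consent (second consent process) and will form the interventional arm".
- **Control arm, first definition.** Study design: "Participants not randomly selected to consider the trial intervention will receive standard of care (partial nephrectomy) and will form the control arm". These patients give no second consent. The same section says that cohort participants are managed at their own and their clinicians' discretion.
- **Control arm, second definition.** Interventions: "The control group will be composed of participants treated with standard of care (partial nephrectomy").
- **Numbers.** Abstract: "The comparator group will be robotic partial nephrectomy (n=25"). Sample size and recruitment: "We will aim to recruit 50 patients into the embedded randomised study, randomised equally between the two groups". That section also gives a 30% consent rate, and then expects to recruit at least 30% of eligible patients, put at 25 a year for 24 months.
- **Analysis.** Statistical methods: "Data will be analysed on an intention-to-treat basis".

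**The concern.** In a design that randomises an offer, the randomised groups are those selected for the offer and those not selected. Intention-to-treat keeps each patient in the group that selection gave. The article uses up to three rules: selection (controls, Study design), treatment received (controls, Interventions) and possibly second consent (interventional arm, Study design). It does not say which arm holds a selected patient who declines.

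Patients who accept may differ systematically from those who decline, and so may controls who have the operation from those who do not. Dropping decliners, or controls who are not operated on, removes the protection of randomisation from the comparisons of complications, costs and quality of life. It also changes counts on which the feasibility conclusion rests. Recruitment is the primary outcome, retention is counted over randomised participants, and the 12-month review, which can end in stopping the trial, compares complications and waiting time between the groups.

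**Working it through.** **Step 1. The plan's recruitment figures.** If 30% of eligible patients gives 25 a year, then 25/0.30 = 83.3 eligible a year. Over 24 months, 50/0.30 = 166.7 eligible give 50 recruited. Blocks of 10 give 50/10 = 5 complete blocks, so exactly 25 against 25 by selection. On this reading the figures agree.

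**Step 2. What the 30% can be a share of.** Let q be the proportion of invited patients who accept. Controls need no second consent, so after 1:1 selection the enrolled share of all those randomised is 0.5 + 0.5q. This is never below 50%, so 30% cannot be that share. It is either acceptance of the invitation or a share counted before randomisation, such as agreement to join the study. The stated precision of ±11% does not settle which. The 95% half-width 1.96 × √(0.3 × 0.7/n) is 18.0% for n = 25, 12.7% for n = 50, 9.8% for n = 84 and 7.0% for n = 167. A half-width of 11% needs n of about 67, which matches none of these candidates. That mismatch is a separate matter and is not pursued here.

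**Step 3. Arm sizes by acceptance rate.** Under 1:1 selection the number of controls equals the number invited. Only the 30% row uses a figure from the article, and only if 30% is acceptance of the invitation. The other rows are assumptions that show the range.

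| q | Consenters from 25 invited (25q) | Invited for 25 consenters (25/q, rounded up) | Controls alongside | Sample size factor (1/q²) |
|---|---|---|---|---|
| 0.30 | 7.5 | 84 | 84 | 11.1 |
| 0.50 | 12.5 | 50 | 50 | 4.0 |
| 0.70 | 17.5 | 36 | 36 | 2.0 |
| 0.90 | 22.5 | 28 | 28 | 1.2 |
| 1.00 | 25 | 25 | 25 | 1.0 |

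Only q = 1 gives 25 consenters against 25 controls in expectation. The chance that all 25 invited accept is q^25: 0.07 at q = 0.90 and 8.5 × 10⁻¹⁴ at q = 0.30.

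The last column applies to the later full trial. It assumes that controls do not receive cryoablation, that the offer has no effect on decliners, and that variances are equal. The intention-to-treat effect is then q times the effect in acceptors, and the sample size grows by 1/q² relative to full acceptance.

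**Step 4. Bias if only consenters are counted.** Suppose acceptors and decliners differ in mean outcome by δ with no treatment effect. The invited group as a whole has the same expected mean as the controls. Acceptors differ from that mean by (1 − q)δ, which is 0.70δ at q = 0.30, 0.50δ at 0.50, 0.30δ at 0.70 and 0.10δ at 0.90. The article gives no basis for a value of δ.

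**Step 5. The 12-month review.** With 25 invited evenly over 24 months, 12.5 are invited by month 12. At q = 0.30, 12.5 × 0.30 = 3.75, so about 4 would have consented to cryoablation.

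**The case against.** The strongest reply is that the article already defines the arms by selection. The grammatical subject of the interventional-arm sentence is the participants randomly selected, and its counterpart is those not selected. Being asked for consent is a step that follows. The n of 25 is attached to those invited, retention counts randomised participants, and the analysis is by intention-to-treat. The treatment-received wording sits under Interventions, where one expects a description of what each group receives. The flow chart, full protocol and analysis plan are not shown and may place decliners explicitly. All analyses are exploratory, and learning the acceptance rate is part of a feasibility study's purpose.

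Much of this stands. Selection is the more natural reading, and 25 against 25 by selection is attainable. A reader might infer that the planned arm sizes are impossible, or that the numbers fit no reading. The documents do not support either, because both claims require 30% to be acceptance of the invitation and the arm to be consenters only. Nor does the article say that only 30% of those offered cryoablation are expected to accept, or that 25 will receive it.

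The reply does not remove two conflicting statements about the control group within the article. That is not an omission left to another document. It also does not make the interventional-arm sentence unambiguous for a patient who is selected, asked and refuses. The exploratory label does not help either, since exploratory estimates still need a defined group.

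**Conclusion.** The point holds as an inconsistency in how the arms are defined, together with an unstated denominator for the 30%. It does not show that the design is unworkable or that intention-to-treat has been abandoned.

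The control group has two definitions, and only the one by random selection agrees with intention-to-treat. The interventional arm has two possible readings, and only the one that includes decliners agrees with it. That conclusion does not depend on the 30%.

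The size is conditional. If 30% is second-stage acceptance, 25 invited give about 7 or 8 consenters, and 25 consenters would take about 84 invited and 84 controls. If 30% is the share of eligible patients recruited, 25 against 25 by selection is coherent, but the article gives no planning value for second-stage acceptance, so the number who will receive cryoablation is unknown. The 11-fold sample size factor and the 0.70δ bias belong to the first reading only and rest on the assumptions in Steps 3 and 4.

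**What to change.** In Study design and Interventions:

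1. Define the intervention arm as all eligible participants randomly selected to be offered cryoablation, whether or not they accept.
2. Define the control arm as all eligible participants not selected, whatever treatment they receive, and delete the clause that composes the control group by treatment received.
3. State that 25 per arm counts participants by random selection.

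In Sample size and recruitment, state the denominator of the 30% consent rate, and give the expected number receiving cryoablation conditional on the acceptance rate. A figure of 7 or 8 should not be written in unless 30% is confirmed as second-stage acceptance.

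Keep intention-to-treat as the primary analysis. A complier-average estimate is optional. Carry the observed acceptance rate into the design of the full trial.

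The cost is wording, and possibly a lower stated number expected to receive cryoablation. First-stage consent already covers long-term follow-up, data linkage and questionnaires, so decliners can be analysed without a new consent. The text should also say which assessment schedule applies to decliners, because the article omits the 4-week assessment for patients outside the second stage and counts their month 6 from baseline.
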